**14. ETHICAL CONSIDERATIONS (including consent process)**

Screening for eligible participation in the trial will take place by phone if a patient contacts the trial site for further information and before written consent. Further screening may be necessary at the first appointment. Prior to a patient’s arrival at the clinic, standardised forms are sent to patients for completion in preparation for the initial physiotherapy assessment. For the purposes of this study, in addition to these forms, two Participant Information Sheets will be sent to the patient; one for them and one for their nominated carer (e.g., spouse). This will inform the potential participants of the Parkinson’s Disease Research project at North Shore Physiotherapy and invite them to read the enclosed information sheet. If patients wish to learn more information, the information sheet will direct them to contact the administrative team at North Shore Physiotherapy and the SAN hospital prior to their appointment. Should a patient indicate an interest in participating, the Principal Coordinating Investigator will contact the patient by phone, answer any questions and further explain the project and determine eligibility to participate in the project. Patients with Parkinson’s Disease as well as their nominated carer will be asked to re-read the Participant Information Sheet and bring the consent form for signing to their first appointment.

A potential participant will have time to consider participation in the trial between receipt of the Participant Information Sheet, the telephone discussion with the Principal Coordinating Investigator and the first appointment. The length of this period can be up to four weeks before an appointment time becomes available.

Participants in Group 2 (sham/placebo treatment) will be offered active light treatment with the active light devices at the conclusion of the 12-week study free of charge.

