DDT, although effective in assisting communication between cells in the impaired mid brain (Calabresi et al., 2015) has many side effects, (more common in the medium term) that may cause alterations in other neural pathways (Ferrazzoli 2016). Identifying alternative non-invasive methods of stimulating cellular activity in neurones within the impaired mid-brain may prove highly beneficial to people with PD.

Physiotherapy has been established as an effective and complementary treatment for the management of PD regardless of medical interventions (Tomlinson et al., 2013). The aim of physiotherapy is to offer strategies and improve strength and capacity for some of the impairments such as gait disturbances, reduced strength, coordination and balance responses, assist in movement initiation strategies and maintain dexterity and fine motor control. Current physiotherapy, therefore, does much to improve the quality of life and functional capacity, however, it is unable to halt disease progression.

Photobiomodulation therapy (PBMt; also known as light therapy, low intensity laser therapy or low-level laser therapy) has been used in humans for a wide range of conditions such as musculoskeletal disorders, inflammatory conditions and neurogenesis. PBMt is a safe, non-invasive, and non-thermal modality that is based on a substantial body of research dating back to the 1960s (Chung, 2012). The mechanisms of action are proposed to involve the stimulation of mitochondria by the absorption of photons in cytochrome c oxidase, resulting in increased ATP production, leading to reduced oxidative stress, anti-inflammatory effects, improved cellular energy, increased synthesis of enzymes, and increased focal cerebral blood flow (Hamblin, 2016). Most encouragingly, recent research has reported neuroprotection against brain cell degeneration, stimulated by PBMt in animal models of PD (Darlot et al, 2016; Johnstone et al 2014, Johnstone et al, 2015).

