**8a. Inclusion criteria**

- Females and males aged 60–85 years
- Diagnosed with Idiopathic PD (by UK Brain Bank Criteria) with Modified Hoehn & Yahr (H&Y) Stage I-III during ON periods
- ≥3weeks of stable anti-Parkinson’s Disease medication.

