**10. RECRUITMENT STRATEGY**

Potential participants will be recruited from specialised private clinics and neurologists at the Sydney Adventist Hospital through paper advertisements and referrals from specialist clinicians.

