**13b. Statistical analysis**

As a series of N=1 studies, it is anticipated that only basic statistical analysis will be performed. For each outcome measure, descriptive data (mean, standard deviation) will be calculated. From this data, “minimally important difference” (MID) scores will be computed based on ½ SD of each measure. This is a common MID measure (Norman et al, 2003) based on the distribution of the participant scores at baseline and provides a sensitive indicator of significant change over time for N=1 case studies. As such, it does not suffer from a lack of statistical power that would be evident with more traditional ANOVA approaches with small sample sizes. The number of participants showing improvement (i.e., difference between two time points > MID) can be compared between time points with chi-square analyses.

Participants showing improvement in the Sydney arm of the multi-centre Parkinson’s trial will be compared to the Brisbane and Adelaide arms (chi-square analysis) in order to establish optimum PBM areas of treatment and doses regimens.

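### Some participants may enter through a physiotherapy intake, yet only medication must be stable and no visible item records physiotherapy, so the written time-point and cross-trial comparisons cannot separate its effect from that of PBMt.

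*Protocol*

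**What the plan says.** **Route in.** Protocol section 14 describes what happens before a patient comes to the clinic: "standardised forms are sent to patients for completion in preparation for the initial physiotherapy assessment". The trial invitation is added to that mailing: "For the purposes of this study, in addition to these forms, two Participant Information Sheets will be sent to the patient". Consent is signed at the first appointment, and on the time to consider taking part the section says: "The length of this period can be up to four weeks before an appointment time becomes available". This is one route among several. Section 10 states: "Potential participants will be recruited from specialised private clinics and neurologists at the Sydney Adventist Hospital through paper advertisements and referrals from specialist clinicians".

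**Status of physiotherapy.** Section 2 says: "Physiotherapy has been established as an effective and complementary treatment for the management of PD regardless of medical interventions". It lists gait, strength, coordination, balance, dexterity and fine motor control among the targets, and adds: "Current physiotherapy, therefore, does much to improve the quality of life and functional capacity".

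**Outcomes.** The primary outcome (10a) is quality of life. The secondary outcomes (10b) include gait and mobility tests, fine motor tests and balance.

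**Stability at entry.** The only background treatment that must be steady is medication: "≥3weeks of stable anti-Parkinson’s Disease medication" (8a). The exclusion criteria (8b), the visit measures, the tool list (12b) and Appendix 8 do not name physiotherapy or exercise.

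**Analysis.** Section 13b calls a participant improved when the difference between two time points exceeds half the baseline SD. The numbers improved "can be compared between time points with chi-square analyses", and Sydney improvers are then compared with those in the Brisbane and Adelaide trials.

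**The concern.** The protocol names two background treatments that it regards as effective, dopaminergic medication and physiotherapy, and holds only the first steady. One stated route of invitation reaches people who are about to be assessed at a physiotherapy clinic, so some may begin physiotherapy close to the trial baseline. Any resulting gain would fall on the outcomes by which PBMt is judged.

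Both comparisons written in 13b count improvement from each participant's own baseline, and neither subtracts what happens in the sham group. A physiotherapy gain and a PBMt gain look the same in such counts. The cross-trial comparison is meant to identify the best treatment areas and dose regimens, so a difference between the trials in physiotherapy use could be read as a difference between light regimens. If physiotherapy is not recorded, no later analysis can examine or adjust for it.

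**Working it through.** The plan states no figure for physiotherapy, so there is none to reproduce. The check asks how far a physiotherapy gain would move the share of participants classed as improved if PBMt did nothing.

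**Inputs from the Protocol.** Improvement threshold 0.5 baseline SD (13b); 20 participants per group (sections 6 and 8c); assessments at weeks 0, 4 and 12 and at 6 months (section 12).

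**Assumptions.** Normal scores with equal SD at both times; retest correlation r of 0.7 to 0.9; physiotherapy gain d of 0, 0.2, 0.3 or 0.5 SD among those who start; half, or a quarter, of participants starting.

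**Formula.** In baseline SD units the change has SD √(2(1 − r)). The improver share is 1 − Φ((0.5 − d)/√(2(1 − r))). At r = 0.8 the change SD is √0.4 = 0.632. With d = 0 the share is 1 − Φ(0.791) = 21.5%; with d = 0.2 it is 1 − Φ(0.474) = 31.8%.

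| r | d = 0 | d = 0.2 | d = 0.3 | d = 0.5 |
|---|---|---|---|---|
| 0.7 | 25.9% | 34.9% | 39.8% | 50.0% |
| 0.8 | 21.5% | 31.8% | 37.6% | 50.0% |
| 0.9 | 13.2% | 25.1% | 32.7% | 50.0% |

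**Rise in the improver share** = proportion starting × (share at d − share at 0).

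- Half starting, r = 0.8: 0.5 × (31.8 − 21.5) = 5.2 points; 0.5 × (37.6 − 21.5) = 8.1 points; 0.5 × (50.0 − 21.5) = 14.3 points.
- Half starting, extremes over r: 0.5 × (34.9 − 25.9) = 4.5 points to 0.5 × (50.0 − 13.2) = 18.4 points.
- A quarter starting: half of those extremes, 2.3 to 9.2 points.

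**Effect on the written time-point test.** This was simulated with 5,000 runs, 20 per arm, no PBMt effect, r = 0.8, one third of the physiotherapy gain present at week 4, and an uncorrected chi-square at 0.05. Comparing week 4 with week 12 improvers in the active arm gives a significant result in about 2% of runs with no physiotherapy gain. The figure is about 6% when half start and gain 0.5 SD, and about 21% when everyone does.

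**Effect on active versus sham.** In the same simulation the active-versus-sham chi-square at week 12 is significant in about 5% of runs when half of each arm start and gain 0.5 SD, and in 4.4% when everyone does. With uneven uptake, 70% in active and 30% in sham, the improver shares are 41.5% and 30.0% and the test is significant in 11.8% of runs.

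**Chance imbalance.** With X₁ and X₂ independent Binomial(20, 0.5), P(|X₁ − X₂| ≥ 4) = 0.268. An imbalance of 4 in 20 shifts the difference in improver share by 0.2 × 10.3 = 2.1 points, 0.2 × 16.1 = 3.2 points or 0.2 × 28.5 = 5.7 points for gains of 0.2, 0.3 and 0.5 SD. At a common share of 26.7% (21.5 + 5.2) the standard error of that difference is √(2 × 0.267 × 0.733/20), about 14 points.

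**The case against.** **No course of physiotherapy is stated.** Section 14 mentions an initial assessment, and physiotherapists also collect outcome measures in this trial (section 6). A reader might infer that new physiotherapy will be counted as a PBMt response. The documents show only that it can be. Section 10 names other routes, and Appendix 8 adds public media recruitment and moves treatment home. Any uptake figure is an assumption. This objection stands and makes the point conditional.

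**Physiotherapy may be recorded somewhere unseen.** The content of the carer diary form, the demographic items and the clinic's own forms is not visible. The supportable statement is that no visible item records physiotherapy, not that nothing does.

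**The sham group absorbs shared background care.** A reader might take the 27% chance of an imbalance of 4 or more starters as a bias. Under random allocation it is not one: the test's error rate already allows for chance imbalance and stays near 5%, and the shift of 2.1 to 5.7 points is small against a standard error of about 14. The uneven-uptake result would matter only if uptake differed systematically between arms, which nothing in the documents suggests. The sections at hand do not show how participants are allocated, and no point is made of that here.

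**The time-point test moves little in moderate cases.** About 6% against 2% is modest, and the 21% needs every participant to gain 0.5 SD. This stands as to significance. It does not answer the rise in the improver counts, which 13b carries into the comparison with the other trials.

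**A statistical analysis plan could add the between-arm test and adjustment.** It could, so their absence is not the finding. It could not add an entry condition, or adjust for a variable that was never collected.

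**Conclusion.** The point holds as a conditional weakness of design. The protocol regards physiotherapy as effective on its own outcome domains, one recruitment route runs through a physiotherapy intake, and the visible text neither holds physiotherapy stable nor records it. The two comparisons written in 13b cannot tell such a gain from a PBMt gain.

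With half of participants starting, r = 0.8 and a gain of 0.2 to 0.5 SD, the improver share rises by about 5 to 14 points in both arms. If only a quarter start, the rise is about 2 to 9 points over r of 0.7 to 0.9. If nobody starts, it is nil. Uptake, gain and retest correlation are all assumed.

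The documents do not support a claim of bias in a randomised active-versus-sham comparison, where the cost is extra noise and an imbalance that cannot be examined. The change is worth making because it is cheap and cannot be made after the data are collected.

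**What to change.** 1. In 8a, extend the existing stability condition to physiotherapy and exercise, so that the programme, or its absence, is unchanged for a set period before baseline. The present medication rule uses at least 3 weeks; the trial team should confirm whether that window suits physiotherapy.
2. Add to the visit measures and to 12b a short question on physiotherapy and exercise (type, frequency, any change), asked at baseline and at each existing visit. Carry the same question into Appendix 8.
3. In 13b, draw the conclusion about PBMt from the active-versus-sham comparison, with a sensitivity analysis that adjusts for physiotherapy status at entry. Present the time-point and cross-trial counts as descriptive.

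**Cost.** Some newly referred patients enter a few weeks later, and each visit carries one more question. Nobody's care during the trial is restricted, and no visit is added.

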**4. OBJECTIVES**

1. to determine the effect of PBMt over a 12-week period on a variety of fine and course motor symptoms
2. to determine the effect of PBMt over a 12-week period, on a cognitive function, including social cognition
3. to determine the effect of PBMt over a 12-week period, on the composition of the intestinal and oral microbiome

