**10b. Secondary Outcomes:**

- Course motor control (up-and-go test; timed walk; step test)
- Fine motor control (spiral test; 9-hole peg test; writing task)
- Balance (static; tandem)
- Cognition (Montreal Cognitive Assessment)
- Self-assessment (PDQ39 questionnaire; PDSS sleep scale)
- Carer diary of daily living
- Smell identification test
- Microbiome analysis

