**12. STUDY PROCEDURES**

**11a. Study procedure**

The PBMt intervention will consist of 3 treatment sessions per week for 12 weeks (Groups 1). Participants in the active treatment group will receive transcranial light treatment with a PDNeuro LED helmet device (parameters given in Appendix 1). The treatment areas are 20 points (

154.5 joules total energy). The treatment time is 24 minutes. Participants in the placebo/sham group (Group 2) will receive the same apparent treatment as Group 1, except that they will be “treated” with sham transcranial LED devices that delivers no light.

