**Outcome** **measures**

Group 1 and 2: Outcome measures will be performed at the commencement of the trial before intervention (baseline, week-0), after 4 weeks of treatment, and at the end of the trial (12 weeks of treatment), and at 6-months (3-months of zero intervention wash out). In addition to the physiognomy measurements (weight, girth), motor coordination, balance, cognition, social cognition, smell test, carer diary and self-assessment outcome measures, participants will also be asked to provide faecal and saliva samples (for microbiome analysis) on 2 occasions; 3 samples before treatment begins and 3 samples at the end of the treatment period (12 weeks).

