**Appendix 8**

Contingency protocol

In the event that the currently proposed protocol is unable to proceed due to uncontrollable and/or unforeseen restrictions or regulations, the following changes will be implemented to the existing protocol constituting a new contingency protocol.

1. **Study design**
   1. Treatment will consist of home-based (in the participant’s own home) PBMt to the head and nose (either active or placebo treatment), 6 daily treatments per week for 12 weeks. Outcome measures to be supervised and data collected via the use of video link by Specialist Examiners and the Physiotherapists.
2. **Study setting/location**
3. Study location for both treatment outcome measures assessments will be changed to the participant’s own home.
4. **Inclusion criteria**
5. In addition to the inclusion criteria already stipulated, eligible participants will require:

   - Sufficient space (around 9 m^2^) to be able to perform motor assessments.
6. - Stable and sufficiently fast home-based internet connection for uninterrupted video calls and video conferencing.

   - Knowledge (self or carer) of using a phone and/or tablet applications on either IOS or Android platforms.**Study procedure**
7. In the absence of researcher/specialist-directed intervention, to ensure blinding of participants from group allocations and to reduce the change of participants inadvertently realising that they are in the sham, participants will be informed that there are 3 groups rather than 2 (Group 1: receiving red and infra-red light; Group 2: receiving infra-red light only; Group 3: receiving sham). In fact, there will remain to be 2 groups (Group 1: receiving red and infra-red light; Group 2: receiving sham).
8. **Outcome measures**
9. Outcome measures will be performed at the commencement of the trial before intervention (baseline, week-0), then after 2, 4, 6, 8, 10-weeks of treatment, and at the end of the trial (12-weeks of treatment), and at 6-months (3-months of zero intervention wash out).
10. All outcome measures will be conducted and recorded using a combination of self-reported assessment, visual assessment via video link with a specialist examiner (during live video or pre-recording by the participant).

1. **Consent process**
2. All previous in-person appointments during the consent process will now be conducted via video-link. For example:

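### The 6-month visit is called a zero-intervention wash-out for both groups, yet the sham group alone is offered active treatment at week 12

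*Protocol*

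**What the plan says.** The Outcome measures paragraph under section 12 sets one schedule for both arms: "Group 1 and 2: Outcome measures will be performed at the commencement of the trial before intervention", then after 4 weeks, then "at the end of the trial (12 weeks of treatment), and at 6-months (3-months of zero intervention wash out". Week 12 is thus named as the end of the trial, and the following three months as free of intervention for Groups 1 and 2 alike. Appendix 8, the contingency protocol, keeps the label: "at 6-months (3-months of zero intervention wash out".

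Section 14 says that Group 2 participants "will be offered active light treatment with the active light devices at the conclusion of the 12-week study free of charge". No such offer is described for Group 1.

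Three other places bear on the point:

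- 11a, Study procedure, sets the regimen at "3 treatment sessions per week for 12 weeks".
- 10b, Secondary Outcomes, includes "Self-assessment (PDQ39 questionnaire; PDSS sleep scale", both self-reported.
- Section 13b counts participants whose change between two time points exceeds half a baseline SD, and says these counts "can be compared between time points with chi-square analyses".

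**The concern.** The wash-out label and the post-trial offer cannot both hold for a sham participant who accepts and starts promptly. Offering sham participants the active device is not itself a fault. The problem is when the offer falls relative to the wash-out.

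Two properties of Group 2's 6-month data are at risk:

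- **Untreated status.** An improver count from week 12 to 6 months, or from baseline to 6 months, could mix the end of sham treatment with new active exposure.
- **Blinding.** An offer made only to Group 2 tells its members, including those who decline, that they had sham. Group 1 members who know of the offer could infer the reverse when none is made to them. This would happen before the 6-month questionnaires, in a trial whose primary outcome is quality of life. Appendix 8 shows how much weight participant blinding carries: participants are to be told that there are three groups so that sham recipients do not recognise their allocation.

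Without an untreated, blinded Group 2, the 6-month visit gives no controlled reading of how long an effect in Group 1 persists.

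**Working it through.** The protocol gives no figure to reproduce here. The check is a comparison of timings, followed by arithmetic on how much exposure fits in the gap.

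**1. Timeline**

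| Time | Group 1 | Group 2 |
|---|---|---|
| Weeks 0–12 | Active | Sham |
| Week 12 | Treatment stops | Treatment stops; active treatment offered (section 14) |
| Week 12 to 6 months | No intervention | Labelled no intervention (section 12, Appendix 8), but active treatment is available |
| 6 months | Assessed about 3 months off treatment | Assessed; may have just finished active treatment |

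The offer falls at the start of the interval labelled as free of intervention.

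**2. Room for exposure (from the document)**

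- One course: 3 × 12 = 36 sessions.
- With the 6-month visit at week 24: (24 − 12) × 3 = 36 sessions.
- With the visit at week 26: (26 − 12) × 3 = 42 sessions.
- Under Appendix 8, at six treatments per week, a course is 6 × 12 = 72 and the gap holds 72 to 84.

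Under either regimen a full course fits. The length of the course offered to Group 2 is not stated, so a repeat of the trial course is an assumption.

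**3. Effect on a 6-month group difference, if one were drawn (illustrative)**

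Let D be the on-treatment effect, k the share of it that Group 1 retains at 6 months, f the share of Group 2 exposed, and e the share of D that those exposed have reached. All four are assumptions. With an untreated Group 2 the difference is kD. With exposure it is (k − f·e)D.

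| k | f | e | No exposure | With exposure |
|---|---|---|---|---|
| 1 | 0.5 | 0.5 | 1.00D | (1 − 0.25)D = 0.75D |
| 1 | 0.5 | 1 | 1.00D | (1 − 0.50)D = 0.50D |
| 0.5 | 0.8 | 0.5 | 0.50D | (0.5 − 0.40)D = 0.10D |
| 0.5 | 0.8 | 1 | 0.50D | (0.5 − 0.80)D = −0.30D |

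The sign reverses only if f·e exceeds k. At f = 0 exposure causes no bias.

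**4. Effect on Group 2's improver count (illustrative)**

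Work in baseline SD units with a threshold of 0.5. Assume D = 0.5, equal SDs at the two visits, normally distributed change, a baseline-to-follow-up correlation of 0.7, and zero mean change in unexposed sham participants (no retained sham response and no progression).

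- SD of change = √(2 × (1 − 0.7)) = 0.775.
- P(change > 0.5) = 0.259 at mean 0, 0.373 at mean 0.25 (e = 0.5), and 0.500 at mean 0.5 (e = 1).
- Expected improvers of 20 = 20 × [(1 − f) × 0.259 + f × p], where p is the probability for those exposed.

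| f | e = 0.5 | e = 1 |
|---|---|---|
| 0 | 5.2 | 5.2 |
| 0.5 | 6.3 | 7.6 |
| 1 | 7.5 | 10.0 |

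Over correlations of 0.6 to 0.8 and D of 0.3 to 0.5 SD, with e at 0.5 or 1, f = 0.5 gives 5.0 to 7.9 improvers, against 4.3 to 5.8 with no exposure.

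**The case against.** The strongest reply is that little hangs on the 6-month visit. The objectives concern effects over 12 weeks (section 4: "to determine the effect of PBMt over a 12-week period on a variety of fine and course motor symptoms", with the others framed alike). No 6-month active-versus-sham test is named, section 13b only permits comparisons between time points, and there is no durability hypothesis. All of that stands. It limits the damage to follow-up data but does not reconcile the two statements.

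Second, an offer is not delivery. No start date, course length or uptake is given, and treatment offered at week 12 could be delivered after the 6-month visit, in which case the label would hold. That is possible, so exposure is conditional. It is not the natural reading, though: section 14 ties the offer to the close of a 12-week study, and section 12 itself calls week 12 the end of the trial. Delayed delivery would also leave the disclosure problem if the offer itself is made at week 12.

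Third, unblinding is inferred, because the protocol does not say how or when allocation is disclosed. That is correct, and whether assessors would learn it is also unstated. Still, it is hard to see how an offer confined to one arm could be made without telling its members which arm they were in. Participant information, which was not available for this review, might set a later time.

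Fourth, the illustrative figures rest on assumed inputs, including zero mean change in unexposed sham participants, and steps 3 and 4 are not evidence about this trial. Agreed: only the session counts come from the document.

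Last, how 6-month data are reported can be left to a statistical analysis plan. But such a plan cannot restore an untreated, blinded group once the offer has been taken up. The timing of the offer is a protocol and consent decision.

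**Conclusion.** The concern holds. As written, the protocol describes Group 2 as free of intervention from week 12 to 6 months and makes active treatment available to it from week 12. Nothing in the text available reconciles the two. Group 2's 6-month data may therefore be neither untreated nor blinded, and cannot be relied on as a control for persistence of effect.

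The firm part of the size is that the gap holds at least one full active course. How far results would shift depends on uptake, start date and the effect itself, none of which is known; with no uptake there is no exposure bias, although early disclosure would remain.

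The week-4 and week-12 comparisons are unaffected, provided the offer follows the week-12 assessment, and so is Group 1's off-treatment status. This should be fixed, but it does not threaten the 12-week results.

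**What to change.** Choose one of two.

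1. **Defer the offer.** State in section 14 and the participant information that active treatment is offered, and allocation disclosed, only after the 6-month assessment. The wash-out label then holds for both groups and the visit supports a controlled, blinded comparison. The cost is one sentence in each place and a wait of about three more months for sham participants.
2. **Keep the week-12 offer.** Remove the zero-intervention label for Group 2 in section 12 and Appendix 8, state that the active-versus-sham comparison ends at week 12, treat the 6-month data as uncontrolled, unblinded follow-up of Group 1, and record each Group 2 participant's date of first active exposure. The cost is two wording changes, a statement on the comparison and one recorded date, and the trial gives up any controlled reading of durability.

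The first option is preferable if persistence of effect is a reason for holding the 6-month visit.
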